### 4.3 Exclusion criteria

A potential subject who meets any of the following criteria will be excluded from participation in this study:

- 1) Patients who died within the first 24 hours due to other injuries than fireworks
- 2) Patients with incomplete or unknown contact information;
- 3) Insufficient understanding of Dutch or English to understand the study documents

### 4.4 Sample size calculation

A report from VeiligheidNL mentions 574 patients during the annual change of year in 2014-2015 in The Netherlands. With 2 full months for inclusion we expect to increase this by at least 10% ( $n=638$ ). The Southwest Netherlands area contains 10 of the 90 Dutch hospitals. This could project to a possible sample of 70-80 patients. A formal sample size calculation for this observational study is not constructive. By including all patients treated in the Trauma Region Southwest Netherlands during the specific time interval, the largest possible sample will be enrolled. The larger the number of patients, the more reliable the analysis will be. Enrolling all patients possible will result in the highest reliability of data (*i.e.*, accurate point estimate with lowest possible variance).

**5. TREATMENT OF SUBJECTS**

Not applicable, this study is not an intervention study.

**5.1 Investigational product/treatment**

Not applicable, this study is not an intervention study.

**5.2 Use of co-intervention (if applicable)**

Not applicable, this study is not an intervention study.

**5.3 Escape medication (if applicable)**

Not applicable, this study is not an intervention study.

**6. INVESTIGATIONAL PRODUCT**

Not applicable, as this study does not involve an investigational product.

**6.1 Name and description of investigational product(s)**

Not applicable, as this study does not involve an investigational product.

**6.2 Summary of findings from non-clinical studies**

Not applicable, as this study does not involve an investigational product.

**6.3 Summary of findings from clinical studies**

Not applicable, as this study does not involve an investigational product.

**6.4 Summary of known and potential risks and benefits**

Not applicable, as this study does not involve an investigational product.

**6.5 Description and justification of route of administration and dosage**

Not applicable, as this study does not involve an investigational product.

**6.6 Dosages, dosage modifications and method of administration**

Not applicable, as this study does not involve an investigational product.

**6.7 Preparation and labelling of Investigational Medicinal Product**

Not applicable, as this study does not involve an investigational product.

**6.8 Drug accountability**

Not applicable, as this study does not involve an investigational product.

**7. NON-INVESTIGATIONAL PRODUCT**

Not applicable, as this study does not involve a non-investigational product.

**7.1 Name and description of non-investigational product(s)**

Not applicable, as this study does not involve a non-investigational product.

**7.2 Summary of findings from non-clinical studies**

Not applicable, as this study does not involve a non-investigational product.

**7.3 Summary of findings from clinical studies**

Not applicable, as this study does not involve a non-investigational product.

**7.4 Summary of known and potential risks and benefits**

Not applicable, as this study does not involve a non-investigational product.

**7.5 Description and justification of route of administration and dosage**

Not applicable, as this study does not involve a non-investigational product.

**7.6 Dosages, dosage modifications and method of administration**

Not applicable, as this study does not involve a non-investigational product.

**7.7 Preparation and labelling of Non Investigational Medicinal Product**

Not applicable, as this study does not involve a non-investigational product.

**7.8 Drug accountability**

Not applicable, as this study does not involve a non-investigational product.

## 8. METHODS

### 8.1 Study parameters/endpoints

#### 8.1.1 Main study parameter/endpoint

The primary outcome measures are the **injury characteristics**. The following variables will be collected:

- Number of injuries
- Body site injured
  - 1) Head/neck (scalp, forehead, orbital, nose, cheek, mouth/lips, chin, ear, or neck)
  - 2) Eye
  - 3) Upper extremity (shoulder, upper arm, elbow, lower arm, wrist, hand palm, hand dorsum, thumb/first webspace, digit 2, 3, 4, 5, or other (text))
  - 4) Lower extremity (hip, upper leg, knee, lower leg, ankle, foot, other (text))
  - 5) Trunk (chest, abdomen, back, pelvis, or other (text))
  - 6) Other (text)
- Injured side (left, right, or not applicable)
- Type of injury per site (including text description)
  - 1) Burn (total body surface area (TBSA) and degree)
  - 2) Globe rupture (open or closed)
  - 3) Intra-ocular foreign body
  - 4) Penetration/perforation
  - 5) Corneal/adnex burn (chemical or thermic)
  - 6) Lens injury
  - 7) Retina injury
  - 8) Choroidal injury
  - 9) Corneal rupture
  - 10) Soft tissue damage (superficial or deep)
  - 11) Fracture/dislocation (fracture location)
  - 12) Amputation (level of amputation))
  - 13) Vascular damage (affected vessel)
  - 14) Neurological damage (affected nerve)
  - 15) Tendon damage (affected tendon)
  - 16) Other (text)

### 8.1.2 Secondary study parameters/endpoints (if applicable)

The following outcomes will serve as secondary outcome measures:

- Number and type of operations
- Duration of hospital admission
- Direct medical and indirect societal costs
- Absence from school
- Quality of life (EuroQol-5D-3L; EQ-5D-3L)
- Health Utilities Index 3; HUI-3 (domains vision and dexterity)
- Visual acuity
- Quick Disabilities of Arm, Shoulder and Hand (*Quick-DASH*)
- Cold Intolerance Severity Scale (CISS)
- Lower Extremity Functional Scale (LEFS)
- Patient and Observer Scar Assessment Scale (POSAS)
- Patient satisfaction with their functional recovery and cosmesis
- How trauma has affected patient's view on the use of consumer fireworks

The **number and type of operations** performed will be extracted from patients' medical file.

- Operation performed (yes or no)
- Total number of operations performed
- Type of first operation (soft tissue care, enucleation, evisceration, amputation, fracture treatment, revascularization, transplantation, reconstruction (skin grafting, flaps, or other (text description)), repair (vessels, nerves, tendons), other (text description), or multiple) (including text details)
- Indications for the second, third and any other subsequent operation (text description)

The total **duration of hospital admission** will be calculated from the dates of admission and discharge from the hospital. Re-admission to a hospital during follow-up will be counted separately.

In order to determine the **direct medical costs** and **indirect societal costs**, patients will be asked to complete a custom-made questionnaire that contains detailed information on both items. Health care costs will include general practice care, medical specialist care, nursing care, physical therapy, hospitalization,

medication, home care, and other costs directly associated with diagnosis, treatment and rehabilitation. The **indirect societal costs** will be calculated by the absence from paid work, production loss without absence from paid work and hindrance in the performance of paid and unpaid work.

School-going patients (and their parents) will be asked to complete a custom-made questionnaire regarding **absence from school**.

The **EuroQol-5D-3L (EQ-5D-3L)** is a validated questionnaire for measuring health-related quality of life (12, 13). The EQ-5D-3L descriptive system consists of five dimensions of health (mobility, self-care, usual activities, pain/discomfort, anxiety/depression), each with three possible answers. Scores are converted to a utility score ranging from zero to one, with lower scores indicating poorer quality of life. The EQ VAS records the respondents self-rated health status on a vertical (0-100) visual analog scale, which should be used together with the descriptive system to build a composite picture of the respondent's health status. Patients aged 16 years or older will complete the EQ-5D-3L themselves. Parents of pediatric patients 4-7 years old will complete the youth proxy version (EQ-5D-3L-Y proxy), and pediatric patients between 8-15 years old will complete the 'youth' version (EQ-5D-3L-Y) by themselves or if necessary with the help of the parents.

For specific injuries we will ask patients to complete additional questionnaires, in order to gain more insights in injury specific outcomes.

For patients with eye injuries:

The **Health Utilities Index Mark 3 (HUI-3), domain vision** (consisting out of 2 questions, each with four possible answers), will be used to assess patients generic health status and health-related quality of life, regarding their eye injury. Patients aged  $\geq 16$  years will complete the HUI-3 themselves. Parents of a pediatric patient ( $< 16$  years) will complete the questionnaire, together with their child if possible.

**Visual acuity** is determined routinely and will be extracted from patient's medical file.

For patients with upper extremity injuries:

The **HUI-3, domain dexterity** (one question with four possible answers) will assess the health-related quality of life regarding upper extremity injuries. Patients aged  $\geq 16$

years will complete the HUI-3 themselves. Parents of a pediatric patient (<16 years) will complete the questionnaire, together with their child if possible.

The **Quick-DASH** is used in order to measure physical function and symptoms in people with any or multiple musculoskeletal disorders in the upper limb. It is scored in two components: the disability/symptom section (11 items, scored 1-5) and the optional high performance sport/music or work modules (each 4 items, scored 1-5). A higher score indicates greater disability (14). Only patients aged  $\geq 16$  years will complete this questionnaire.

The **Cold Intolerance Symptoms Severity (CISS)** questionnaire is a 6-item questionnaire. The sum of all questions (range 4-100) defines the severity of cold intolerance, with a higher number representing more severe symptoms (15, 16). Only patients aged  $\geq 16$  year will complete this questionnaire.

For patients with lower extremity injury:

The **Lower Extremity Functional Scale (LEFS)** is a validated questionnaire containing 20 items about a person's ability to perform everyday tasks. It can be used to evaluate the functional impairment of a patient with a disorder of one or both lower extremities. All items are scored so that a high score represents greater disability. The maximum score achievable is 80 points (17, 18). Only patients aged  $\geq 16$  year will complete this questionnaire.

For patients with burn wounds

The **Patient and Observer Scar Assessment Scale (POSAS v2.0;** [www.posas.org](http://www.posas.org)) (19) consists of two parts: a Patient Scale and an Observer Scale, which aim to provide a rating of several measured of scar quality (vascularity, pigmentation, relief/texture, thickness, pliability, surface area, pain, and itching/pruritus). Adult patients and parents of pediatric patients (<16 years) will complete the patient-reported part. A trained observer will complete the observer-reported part.

**Satisfaction level regarding function and cosmesis** of the injured area will be determined using an 11-point numeric rating scale, ranging from 0 (extremely dissatisfied) to 10 (fully satisfied). Only patients aged  $\geq 16$  year will complete this questionnaire.

Patients will also be asked to complete a custom-made questionnaire investigating their **view on the use of consumer fireworks** before and after trauma, and how the trauma influenced their opinion. Only patients aged  $\geq 16$  year will complete this questionnaire.

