### Secondary Objective(s):

- 1) To determine the **number and type of operations** needed due to fireworks-related injuries until one year after trauma
- 2) To determine the **duration of hospital admission** in these patients
- 3) To determine the **direct medical costs** and the **indirect societal costs (incl. work absence)** in these patients
- 4) To investigate the **absence from school** in these patients
- 5) To investigate the **patient-reported outcomes** in these patients
  - EuroQol-5D (EQ-5D-3L)
  - Health Utility Index Mark 3 (domains for vision and dexterity) (HUI-3)
  - *Quick* Disabilities of the Arm, Shoulder and Hand (*Quick*-DASH)
  - Cold Intolerance Symptoms Severity (CISS)
  - Lower Extremity Functional Scale (LEFS)
  - Patient and Observer Scar Assessment Scale (POSAS)
  - Patient satisfaction with the functional recovery and cosmesis
- 6) To investigate how the injury changed **patient's view on the use of fireworks**

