#### Treatment characteristics to be collected:

- Prehospital transport (ambulance, Helicopter Emergency Medical Services (HEMS), self-transport, other (text), or unknown)

- HEMS assistance (yes, no, or unknown)
- Referral to hospital (direct or indirect (general practitioner, general practice center, other hospital, or other (text)))
- Admission (yes or no)
- Required care (ward, Intensive Care Unit (ICU), observatory, or other)
- Wound treatment (wound dressings (text), topical therapy (text), other (text), unknown, or not needed)
- Number of transfusions required (packed-cells, platelets, plasma, colloid, or other (text description))
- Discharge destination (home, other hospital, nursing home, rehabilitation facility, burn center, or other)
- Need for prosthesis (yes or no, and description)

Outcome-related variables to be collected:

- Time between initial injury and hospital presentation (calculated from dates of trauma and hospital presentation)
- Duration of hospital admission (calculated from date of admission and date of discharge)
- Duration of ICU admission (in days) (calculated from dates of admission and discharge)
- Mortality (fireworks-related, yes or no)
- Rehabilitation (physical therapy, hand therapy, ergotherapy, other (text description), or multiple)
- Complications and secondary interventions (text description)

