#### B: Data collection

Patients will be followed for one year, with the first visit for baseline measurement planned as soon as possible, preferably within two weeks. Follow-up visits are planned at three months (window 2-4 months), six months (5-7 months), and 12 months (window 12-14 months) after presentation.. In case of early discharge from clinical treatment/follow-up, subsequent follow-up can be performed by visiting patients at home.

The study will not interfere with treatment or follow-up. Data concerning patient characteristics, injury characteristics, treatment details, and clinical outcome data will be extracted from the patient file as much as possible. These data will be collected from the patient's medical files as soon as possible after signing informed consent. For the purpose of the study, additional details concerning treatment and outcome (see paragraph 8) that are not mentioned in the patient's hospital files, will be registered on the case report forms directly. This will be done at the follow-up visits.

As soon as possible and within two weeks after inclusion patients will be asked to complete the questionnaire's, reflecting their pre-injury health status. For all participants this will be the EQ-5D-3L questionnaire. For patients with eye trauma the HUI-3 (domain vision), for patients with upper extremity trauma the HUI-3 (domain dexterity), the *Quick-DASH*, and CISS, for patients with lower extremity trauma the LEFS, and for patients with burn wounds the POSAS. At three, six and 12 months, treatment characteristics, health care consumption details and patient reported outcomes will be collected.

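### Operation type is coded for the first operation only, although secondary objective 1 asks for number and type of operations up to one year

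*Protocol*

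**What the plan says.** Section 2 (Secondary Objectives, item 1) sets the target as number and type of operations "needed due to fireworks-related injuries until one year after trauma". It does not confine type to the initial procedure.

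Section 8.1.2 repeats number and type as a secondary outcome and states that those "performed will be extracted from patients' medical file". It then lists four variables:

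- whether any operation was done;
- "Total number of operations performed";
- "Type of first operation (soft tissue care, enucleation, evisceration, amputation, fracture treatment, revascularization, transplantation, reconstruction" and further categories, with text details;
- "Indications for the second, third and any other subsequent operation (text description".

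Section 8.1.3, among the outcome-related variables, adds "Complications and secondary interventions (text description".

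Section 8.3 B fixes the timing: "At three, six and 12 months, treatment characteristics, health care consumption details and patient reported outcomes will be collected". Section 10.2 has secondary outcomes reported in the same way as the primary ones, so under section 10.1 a categorical outcome appears as number with percentage.

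**The concern.** An indication and a procedure type are different data. The indication gives the reason for going back to theatre; the type says which procedure was carried out. The list moves from type to indication at exactly the point where follow-up begins to add information, the second and later operations.

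At stake is what the type table describes. The reader of objective 1 expects a profile of surgery over the first year. If only the first operation carries a code, the table is a profile of first operations. A graft, flap, nerve or tendon repair, or amputation done at a later operation would add to the total count but to no type category. The introduction justifies the study by the lack of detailed long-term knowledge on treatment, and the one-year follow-up is meant to supply it.

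**Working it through.** The question is which variables are collected, and the protocol states no figure to reproduce. The check sets the objective against the list, component by component.

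| Component of objective 1 | Variable in the protocol | Covered? |
|---|---|---|
| Any operation | Yes/no item, 8.1.2 | Yes |
| Number of operations | Total count, 8.1.2 | Yes |
| Type, first operation | Coded list with text details, 8.1.2 | Yes |
| Type, second and later operations | No type item; free-text indication (8.1.2) and free-text complications and secondary interventions (8.1.3) | Not coded |

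**Can another section fill the last row?** The treatment characteristics in 8.1.3, collected again at 3, 6 and 12 months, contain no operation type. Section 12.2 names patient files and case report forms as source data for surgical details. That says where the information sits, not which item is to be extracted.

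**Can the planned table be made?** A number-with-percentage table needs a category for each unit counted. The list supplies one for each patient's first operation and none for any later operation.

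**How large is the gap?** Let k be the mean number of operations per operated patient. Each operated patient has one operation with a coded type, so the share of operations without one is (k − 1)/k. The protocol gives no value of k, so the following are assumptions and not estimates for this study:

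- k = 1.1: 0.1/1.1 = 9%
- k = 1.5: 0.5/1.5 = 33%
- k = 2: 1/2 = 50%
- k = 3: 2/3 = 67%

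The share runs from small to large over this range, and the documents do not say where the study would fall. Section 4.4 expects 70 to 80 patients in all but does not say how many will be operated on, or how often.

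**The case against.** The strongest reply is that the information is not lost. The lead sentence in 8.1.2 has number and type taken from the medical file without limiting this to the first operation. Section 8.3 B also allows treatment details missing from the file to be entered on the case report form. The free-text field in 8.1.3 can hold what was done. With 70 to 80 patients expected, and only the re-operated ones affected, someone could code the text afterwards from the existing list. The case report form itself is not available and may hold more than the protocol lists.

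Much of this stands, and it rules out several stronger readings that a reader might infer:

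- **That objective 1 cannot be answered.** The count is complete, the first type is coded, and later types can be retrieved.
- **That later operations get nothing but an indication.** The 8.1.3 field is a second place where they may appear.
- **That the type table would describe acute surgery only.** The first-operation list itself includes reconstruction, transplantation, repair of vessels, nerves and tendons, and a category for multiple procedures. Nothing limits a first operation to the acute phase.
- **That the costing fails.** Section 8.1.2 bases costs on a custom-made patient questionnaire, and no section says that operations are costed by coded type. An effect on costs is an inference.

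What the reply does not remove is the mismatch between the objective and the list. Coding after the fact, from free text or from the files of about 10 hospitals, would have no stated rule, although the protocol already has a category list that could serve as one. An analysis plan could define how to code such text, but it cannot ensure that a text field asking for the indication records the procedure.

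**Conclusion.** The point holds in a limited form. The protocol states a collection rule that falls short of its own objective: type is coded for first operations only, so the part of objective 1 that concerns type up to one year is only partly specified. Followed as written, the planned type table would cover first operations and leave out procedures done later.

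The reach is narrow. One component of one descriptive secondary outcome is affected, and only through patients with more than one operation. The primary outcome (injury characteristics) and the number of operations are untouched. The size cannot be stated from the documents. The conclusion assumes that the case report form follows the list in 8.1.2; if it already records a type for every operation, only the protocol text needs correcting.

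**What to change.** In section 8.1.2, replace the item on the type of the first operation with the type of each operation, using the same category list, and record the date and indication of each. In section 10.2, state that type is reported over all operations to 12 months. The date also lets the one-year limit be applied consistently, since the window for the last visit runs from 12 to 14 months.

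The cost is slightly more extraction from the medical file already used for the count, limited to patients with more than one operation. Patients have nothing more to complete, and treatment is unaffected.

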## 1. INTRODUCTION AND RATIONALE

Fireworks are used for celebrating all kinds of rituals and events worldwide. Despite their nice visible and audible effects, it has the potential to cause serious injuries.

Fireworks-related injuries occur frequent in both adults and children. It can be considered a public health problem as they often entail serious and avoidable injuries and often affect innocent bystanders (1-3).

In the USA, the Consumer Product Safety Commission (CPSC) presented a report stating that in 2015 approximately 12,000 fireworks-related injuries were treated in Emergency Departments (ED), reflecting an annual incidence rate of 3.7 per 100,000 individuals. Most patients were males (61%) and 42% were younger than 20 years of age (4). This is comparable with the results of several other studies (1-3, 5-9).

The percentages presented by the CPSC are comparable with the Netherlands with an incidence rate of 2.8 per 100.000 individuals per year treated at an ED with fireworks-related injuries(8). In 36% of the cases, victims were younger than 20 years of age and 76% were males. In the past ten years the number of fireworks-related injuries fluctuates between 400 and 1,000 cases annually. A clear up or downward trend is not observed in the past decade (8).

In two-thirds of all patients, the injuries are located at the hands, face and eyes, mostly consisting out of burns, superficial injuries, and open wounds (2, 5-8, 10, 11).

Most firework-related injuries are non-fatal but they do have the potential to result in long-term disability (3, 5, 8, 10). This has a great effect on the individuals' quality of life and the use of public health services, with high direct medical and indirect societal costs. A Dutch report published in 2016, calculated that the direct medical costs of an individual visiting the ED/admitted to the hospital with a fireworks-related injury are on average €1.600 per individual, based on the years 2011 – 2016, with annual costs of around €1.1 million. When the indirect costs due to absence from work are included as well, this estimate rose to €8.100 per individual and to €2.9 million annually (8).

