## 4. STUDY POPULATION

### 4.1 Population (base)

All patients (no age limit) with fireworks-related injuries presenting to a hospital in the period between December 1, 2017 and January 31, 2018 in the Trauma Region Southwest Netherlands, will be eligible for inclusion. Patients will be recruited from every hospital in the Trauma Region Southwest Netherlands. In the Netherlands it is only permitted to lit fireworks as a consumer during the celebration of New Year's Eve and logically most fireworks-related injuries occur during that night or the period close before and after. Therefore, this specific time range was chosen.

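### Indirect societal costs omit parents' and caregivers' lost work, and the note to Table 1 keeps under-16s off the cost questionnaire, so the mean is not a societal cost for an all-ages cohort

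*Protocol*

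**What the plan says.** Protocol section 2 lists as a secondary objective the direct medical costs and "indirect societal costs (incl. work absence"). Section 8.1.2 says how these are obtained: "patients will be asked to complete a custom-made questionnaire that contains detailed information on both items". The indirect part is then calculated from "absence from paid work, production loss without absence from paid work and hindrance in the performance of paid and unpaid work". All of these are work losses. The text does not say whose work is meant, and parents are not mentioned.

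The next sentence does name parents, for a different outcome: "School-going patients (and their parents) will be asked to complete a custom-made questionnaire regarding" school absence. That is a separate secondary outcome and is not listed as a cost component.

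The note under Table 1 (section 8.3) says that paediatric versions exist for the EQ-5D and HUI-3 and that parents complete the POSAS. All other questionnaires are for patients of 16 and over. Table 1 has one row covering work or school absence together, and none for a parent's or caregiver's work.

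Section 4.1 admits "All patients (no age limit) with fireworks-related injuries presenting to a hospital". Section 10.2 reports costs as a mean with a bootstrap 95% CI, section 10 rules out imputation, and section 10.1 names reporting groups by injury type but not by age.

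**The concern.** When a child is injured, much of the productivity loss may fall on a parent who stays home or attends appointments. An outcome called societal should either count that loss or say that it does not. Here the component is absent from the definition, and the document is unclear on whether children's families receive the cost questionnaire at all.

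The introduction gives long-term societal cost as one of the gaps the study is to fill, to inform the debate on consumer fireworks, and section 11.4 says the study cannot be done without paediatric patients. A mean that leaves out the loss arising from children's injuries, or leaves out the children, would be read as covering everyone. The bootstrap interval reflects sampling variation only and would not reveal either problem. Parental work loss that is not asked about at the visits cannot be recovered in the analysis.

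**Working it through.** The protocol states no figure for this outcome that could be reproduced. The check is a comparison of the sections, followed by an illustration of direction and scale.

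**1. What the sections allow for a patient under 16**

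- *Reading 1.* Section 8.1.2 is applied to every patient and only the patient's own work counts. A child has little or no paid work. Hindrance in unpaid work could still apply, so the child's indirect cost is small rather than strictly zero.
- *Reading 2.* The Table 1 note is applied literally. Under-16s do not complete the cost questionnaire, so their values are missing. With no imputation, the mean covers patients of 16 and over. Direct and indirect costs share this questionnaire, so self-reported direct costs would be missing too.
- *Reading 3.* Parents' work is already asked about on the custom-made form. Neither problem then arises, but no sentence in the protocol says so.

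The Table 1 note cannot be wholly literal, because section 8.1.2 gives school-going patients and their parents an absence questionnaire. The two places need reconciling whichever reading was intended.

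**2. Direction and scale**

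Let A be the mean indirect cost of patients with work of their own, c the share of patients without it, and f the parental work loss per child as a fraction of A. A child's own indirect cost is set to zero for simplicity.

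- Mean with parental loss counted: M = (1 − c)A + c·f·A = A(1 − c + cf)
- Reading 1 gives (1 − c)A, a shortfall of cf / (1 − c + cf)
- Reading 2 gives A, an excess of 1 / (1 − c + cf) − 1

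Inputs: neither c nor f is in the protocol. The introduction says "In 36% of the cases, victims were younger than 20 years of age and 76% were males". That is the share under 20, so 36% can serve only as a ceiling for the under-16 share, and only if the enrolled mix resembles the background population. The assumed ranges are c = 0.15 to 0.36 and f = 0.1 to 1.

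| c | f | 1 − c + cf | Reading 1: mean too low by | Reading 2: mean too high by |
|---|---|---|---|---|
| 0.15 | 0.1 | 0.865 | 0.015/0.865 = 1.7% | 1/0.865 − 1 = 15.6% |
| 0.15 | 1 | 1.000 | 0.15/1 = 15.0% | 0% |
| 0.25 | 0.5 | 0.875 | 0.125/0.875 = 14.3% | 1/0.875 − 1 = 14.3% |
| 0.36 | 0.1 | 0.676 | 0.036/0.676 = 5.3% | 1/0.676 − 1 = 47.9% |
| 0.36 | 1 | 1.000 | 0.36/1 = 36.0% | 0% |

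If f = 0, or under reading 3, the reading 1 shortfall is 0%. With the 70 to 80 patients projected in section 4.4, these shares are about 11 (0.15 × 70 = 10.5) to 29 (0.36 × 80 = 28.8) patients.

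**3. Can the background costs supply a euro figure?**

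The introduction gives direct costs "on average €1.600 per individual" and about €1.1 million a year, which implies 1,100,000 / 1,600 ≈ 688 people. With work absence included it gives €8,100 per person and €2.9 million a year, which implies 2,900,000 / 8,100 ≈ 358 people. The two averages do not share a denominator, so their difference is not a usable indirect cost per patient.

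**The case against.** The strongest reply is that silence is not exclusion. Section 8.1.2 never says whose work is counted, the items of the custom-made questionnaire are not shown, parents already answer on school absence, and Table 1 puts work and school absence in one row. Parental work loss may therefore already be collected, and detailed cost items are often left to the form or the analysis plan. This stands as far as it goes, and it is why the conclusion is conditional. It does not remove the point: the protocol names parents where it wants their answers and does not name them for costs, and the Table 1 note points the other way.

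Two stronger inferences are tempting and not supported. A reader might conclude that the mean societal cost is understated. That holds under reading 1 only; under reading 2 the children are absent, and the figure would be too high for the whole cohort if parental loss per child is below A. A reader might also put a euro amount on the error. The protocol gives no under-16 share and no parental loss, and the background averages cannot be subtracted. Nor is a mean that falls as more children enrol biased for that reason alone; only uncounted loss is bias.

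Two further replies limit the weight of the point. Costs are a secondary, descriptive outcome with no decision rule. Section 10.1 also leaves further subgroups open, so an age split is possible, although without the parental items it would merely show low indirect costs in children.

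**Conclusion.** The point holds as a defect in the definition and collection of a secondary outcome. The listed components do not include parents' or caregivers' lost work, and the Table 1 note read literally keeps under-16s off the cost questionnaire. Followed as written, children either contribute little indirect cost or are missing from the mean, and neither gives a societal cost for a cohort without an age limit.

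The direction of the error depends on which reading is followed, and its size cannot be derived from the protocol. The percentages shown rest on assumed values of c and f and on setting children's own indirect cost to zero; they show only that the effect could range from trivial to substantial. If the questionnaire already covers parents' work for all under-16s, what remains is to say so and to correct the Table 1 note.

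**What to change.** 1. In section 8.1.2, add to the indirect cost components, for patients under 16, absence from paid work of parents or caregivers because of the injury.
2. Collect it with one or two items on the work or school absence form that parents complete, at 3, 6 and 12 months. The items should also reach parents of children not yet at school, whom a form for school-going patients would miss.
3. Amend the note under Table 1 so that parents complete the cost questionnaire for under-16s, in line with section 8.1.2.
4. In section 10.2, report mean indirect cost for under 16 and for 16 and over, as well as pooled, with the number contributing to each.

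The cost is about a minute of extra burden for parents at each of three visits. The other changes are to wording and reporting.
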